**Methods/Design:**

This study is the protocol for a two-armed parallel, assessor-blinded, multicenter, randomized controlled trial. A total 108 patients with chronic neck pain (time to onset ≥ 3 months, numeric rating scale [NRS] of neck pain ≥ 5) will be recruited at five Korean medicine hospital sites. Participants will be allotted to one of two groups (*n* = 54, respectively): the Chuna manual therapy group, and the usual care (conventional physical therapy and medication treatment) group. Ten sessions of Chuna manual therapy or usual care will be administered twice a week for five weeks. Since the study design does not permit patient or physician blinding, the outcome assessor and statistician will be blinded. The primary outcome will be the visual analogue scale (VAS) of neck pain at 5 weeks after randomization. Secondary outcomes include the VAS of radiating arm pain, NRS of neck pain and radiating arm pain, Vernon-Mior neck disability index (NDI), Northwick Park neck pain questionnaire (NPQ), EuroQol-5 Dimension (EQ-5D), EQ-VAS, patient global impression of change (PGIC), economic evaluation, adverse effects, and drug consumption. Follow-up outcome assessments will be conducted at 3, 6, 9, and 12 months after randomization.

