### Blinding

Since it is not feasible to double-blind the practitioner and participant regarding allocation to the two types of treatment due to the study design, blinding of the outcome assessors and statistician will be performed. The outcome assessor will not partake in treatment and a clinical research nurse or a Korean medicine doctor blinded to group allocation will evaluate the participant in a separate area before treatment, and will not try to guess the treatment allocation group to which the participant may be allocated. Computerized data passed on to the statistician will not contain any information identifying patient allocation to either of the two groups.

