#### Co-interventions

No additional treatment (Korean medicine treatment, conventional medicine medication or procedures, physical or exercise therapy) to the purpose of relieving pain other than the treatment provided in the study will be allowed over the course of treatment until the sixth week which is the primary endpoint. However, the research will set no limits after the sixth week. In case the participants in the experimental or control groups experience severe pain during the study period, administration of acetaminophen (maximum dosage of 4 g per day) will be allowed as a rescue medication due to ethical issues. Its use will be specifically reflected and assessed in describing outcomes in the results paper.

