### Outcomes

#### Primary outcome measurement

The primary outcome will be the visual analogue scale (VAS) of the past three days’ neck pain. VAS refers to an evaluation tool that records the degree of pain the patient feels with one end indicating no pain and the other end indicating the most severe pain imaginable on a 100 mm line [18, 19]. Participants will be asked to mark the one point that best describes his or her neck pain during the previous week.

The difference in VAS at baseline (visit 2) and the primary endpoint (follow-up 1 [visit 11]: five weeks after visit 2) will be used to compare the two groups to identify the difference in effect size.

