### Statistical analysis

The main evaluation method will be by intention-to-treat (ITT) analysis that evaluates participants who received at least one session of treatment. Per-protocol (PP) analysis will also be performed, which analyzes only participants who complete participation in the clinical trial in the initial allocated group, excluding participants who withdrew or crossed over during the study. Missing values will be processed mainly by multiple imputation, and last observation carried forward (LOCF) will be used for sensitivity analysis. Participants who received ≥ 6 sessions of treatment during the five-week treatment period will be analyzed separately.

The sociodemographic characteristics and treatment expectancy of participants will be evaluated by group. Continuous variables will be presented as average (standard deviation) or median values (quartile), and the two groups will be compared using Student’s t-test. Wilcoxon rank-sum test will be conducted if the data do not follow normal distribution. Categorical variables will be presented as frequency values (%), and Chi-square test or Fisher’s exact test will be performed as appropriate.

The efficacy variable for this clinical trial is the difference in continuous outcomes (i.e. NRS, VAS, NDI, NPQ, EQ-5D-5 L, SF-12) between baseline and predetermined timepoints. The primary endpoint is one week after completion of treatment (seven weeks after random allocation). Baseline values of each outcome and covariant factors which show statistical difference between groups at baseline will be set as covariates, and analysis of covariance (ANCOVA) with the treatment groups designated as the fixed factor. In addition, to examine the trend difference by visit, repeated measure (RM) ANCOVA will be performed.

To compare the total difference in outcome between the two groups within the treatment period (six weeks) and total study period (one year), the area under the curve (AUC) by specific timepoint after random allocation will be calculated and compared using the Student’s t-test.

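### The primary endpoint time is stated inconsistently: week 5 in the abstract and outcome section, the sixth week under co-interventions, week 7 in the analysis section

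*Protocol article*

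**What the plan says.** Four places in the protocol article give the time of the primary endpoint.

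- **Abstract, Methods/Design:** "The primary outcome will be the visual analogue scale (VAS) of neck pain at 5 weeks after randomization".
- **Primary outcome measurement:** the change in VAS from baseline at visit 2 to "the primary endpoint (follow-up 1 [visit 11]: five weeks after visit 2").
- **Co-interventions:** other pain treatment is not permitted "over the course of treatment until the sixth week which is the primary endpoint", and no limits apply after the sixth week.
- **Statistical analysis:** "The primary endpoint is one week after completion of treatment (seven weeks after random allocation").

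The length of treatment is also given in two ways. The abstract, the trial design, both intervention sections, the sample size section and the first paragraph of Statistical analysis all give five weeks. The AUC paragraph of Statistical analysis compares the groups "within the treatment period (six weeks) and total study period (one year").

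On visits, Trial design and study setting makes the first visit the screening visit, with treatment from the second visit onward. The Blinding section says the assessor "will evaluate the participant in a separate area before treatment".

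**The concern.** The trial has one primary comparison, and the section that an analyst would follow dates it differently from the section that defines the outcome.

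The dates differ in kind as well as in number. Five weeks is the end of the treatment course. The analysis section describes a time after treatment has stopped. An effect at the end of treatment and an effect that persists afterwards are different quantities. At week 7, participants would also have been free to use other pain treatment, because the restriction ends with the sixth week.

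While two times stand in the text, either could be called primary after the data are seen, and a reader of the results could not tell from this article whether the plan had been followed.

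**Working it through.** **1. Nominal times, with randomization as week 0**

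| Place in the article | Stated time | Week |
|---|---|---|
| Abstract | from randomization | 5 |
| Primary outcome measurement | from visit 2 | 5 |
| Co-interventions | the sixth week | 5 to 6 |
| Statistical analysis, in brackets | from random allocation | 7 |
| Statistical analysis, in words | end of treatment + 1 week | 5 + 1 = 6, or 6 + 1 = 7 |

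The last row is not a separate time. It equals week 6 with the five-week course and week 7 with the six-week period of the AUC paragraph. The distinct nominal times are therefore three: 5, 6 and 7.

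**2. Which of them truly conflict**

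- The sixth week, read as an ordinal, runs from day 5 × 7 = 35 to day 6 × 7 = 42. Its start coincides with five completed weeks, so it can be squared with week 5.
- Week 5 is day 35 and week 7 is day 49. The abstract and the analysis section both count from randomization, so no choice of origin closes the 14-day gap.
- Day 49 lies beyond day 42, so it falls after the co-treatment restriction on either reading of the sixth week.

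**3. The visit label**

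Visit 1 is screening. If each of the ten sessions is one visit starting at visit 2, the sessions fill visits 2 to 11. With alternating gaps of 3 and 4 days (an assumption; the article gives only twice a week), they fall on days 0, 3, 7, 10, 14, 17, 21, 24, 28 and 31. Visit 11 would then be the tenth session, at about day 31 (31/7 = 4.4 weeks), whereas the outcome section dates it at five weeks and calls it a follow-up. The text does not settle which is meant.

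**4. Sample size**

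Inputs from the Sample size section: standardized effect 0.6, α = 0.05, power 80%, with 1:1 allocation. Sidedness is not stated; two-sided is assumed. The two-sample t-test (noncentral t) gives n = 44.59, so 45 per group and 90 in total, as stated, with power 80.4% at 45 per group. Inflation for 85% compliance: 45/0.85 = 52.9, so 53 per group or 106, against the stated 108, which is close. None of these inputs depends on the endpoint week.

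**5. Hypothetical effect of choosing between weeks 5 and 7**

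Suppose VAS were collected at both times, each comparison were tested two-sided at 0.05, and the better result were reported. With Z₁ and Z₂ bivariate normal with correlation ρ under no effect, the type I error is 1 − P(|Z₁| < 1.96 and |Z₂| < 1.96):

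| ρ (assumed) | Type I error |
|---|---|
| 0.7 | 8.3% |
| 0.8 | 7.8% |
| 0.9 | 7.0% |

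**The case against.** The strongest reply is that the endpoint is defined. The section whose job is to define it gives an explicit comparison, visit 2 against visit 11 at five weeks, and the abstract agrees. On that view the analysis section carries a slip. This stands in part: the endpoint is defined and then contradicted, and a reader who inferred that it is undefined, or that four separate times compete, would be going too far. It does not remove the contradiction. Figures 1 and 2 are not shown and may indicate the intended visit, but no figure can make five and seven weeks from randomization agree.

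Three further inferences are tempting, and the article does not support them as established facts.

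- **The primary VAS is taken after only nine sessions.** This combines the visit count, an assumed session spacing and a general sentence about blinding, and applies them to a visit the article calls a follow-up. It is a fair question, not a demonstrated fault.
- **Type I error is inflated.** No section schedules separate VAS assessments at weeks 5, 6 and 7. The text names follow-up 1 and then 3, 6, 9 and 12 months. If a single assessment carries inconsistent labels, there is nothing to choose between and no inflation from this source.
- **Power is lost at week 7.** This needs the effect to fade after treatment ends. The article gives no figure for fading, and the effect might equally hold.

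**Conclusion.** The inconsistency is real and should be corrected, because it concerns the only primary comparison. The conflict that cannot be reconciled is week 5 against week 7, a difference of 14 days. The analysis section adds an internal error: its verbal definition gives week 6 under the five-week course stated in that same section, and reaches week 7 only through a six-week treatment period that conflicts with every other statement of duration.

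The consequence is an ambiguous estimand: end of treatment, or a later time that lies outside the period of restricted co-treatment. This rests on the text alone and needs no assumption. The 7 to 8% type I error is conditional on VAS being collected at both weeks, on selection of the better result, and on correlations of 0.7 to 0.9, none of which the article establishes. No power loss is claimed, and the stated 90 and 108 do not change.

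**What to change.** - State one primary time, in days from randomization with a visit window, in identical terms in the abstract, Co-interventions, Primary outcome measurement and Statistical analysis. The abstract and the outcome section already agree on week 5, so the analysis section is the one to change unless the full protocol says otherwise.
- Declare any other assessment time secondary.
- Correct the AUC paragraph so that its treatment period agrees with the five weeks given elsewhere. If the AUC is meant to run to six weeks, describe that as an analysis window and not as the treatment period.
- Reconcile the Co-interventions passage with the chosen primary time.
- State whether visit 11 is the tenth session or a separate follow-up visit and, if it is the session, whether the VAS is taken before or after it.

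The cost is a wording amendment, carried into the statistical analysis plan if one exists. It needs no additional participants or data and changes no sample size figure. If outcome data have already been seen, the amendment should say so and cite the dated full protocol as the source of the chosen time.

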### Trial design and study setting

This study is a two-armed parallel multicenter RCT with assessor-blinding. The study participants will be randomly allocated to one of two groups—the Chuna manual therapy group or the usual care group—at a ratio of 1:1. Participants will be recruited at five Korean medicine hospitals in Korea (Jaseng Hospital of Korean medicine sites located in Seoul, Bucheon, Daejeon, and Busan, and Kyunghee University Korean medicine Hospital at Gangdong located in Seoul) from October 2017 to June 2018 (anticipated). Flyers advertising study participant recruitment will be posted within the hospital grounds and on the hospital and external websites. Further information on the medical institutions acting as the study settings recruiting study participants can be found at the following trial registration sites (Clinical Research Information Service [CRIS] KCT0002732 [https://cris.nih.go.kr/cris/search/search_result_st01.jsp?seq=9719] and ClinicalTrials.gov NCT03294785 [https://clinicaltrials.gov/ct2/show/NCT03294785]). A total of 108 participants with pain and/or discomfort of the neck and surrounding area (trapezius muscle area) will be recruited regardless of accompanying radiating arm pain. Participants will receive treatment twice a week over a period of five weeks in the outpatient department. On their first visit, participants will be screened for study eligibility according to study inclusion and exclusion criteria; from the second visit onward, participants will receive the neck pain treatment relevant to their random allocation group. All study interventions, participants, and execution will be managed in accordance with the study protocol (Figs. 1 and 2).

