### Randomization and allocation concealment

Stratified block randomization will be conducted with stratification by each study site to help control for potential bias in the control and experimental groups. Upon randomization within each study site, participants will be allocated to either the control or experimental group according to the allocation code, and the number of participants in each group will be identical between groups for all study sites.

Random allocation will be performed by a statistician by randomly allocating 54 participants to each group under the condition where the possibility of being chosen is identical for all individuals using SAS version 9.4 statistical package (SAS institute, Cary, NC, USA). The number of participants for each study site will be 24 for Jaseng Hospital of Korean medicine Gangnam branch, 22, respectively for Jaseng Hospital of Korean medicine Bucheon, Daejeon, and Haeundae branches, and 18 for Kyunghee University Korean medicine Hospital at Gangdong. The results of random allocation will each be sealed in opaque envelopes before being sent to each study site and will be kept stored in double lock cabinets.

The researchers responsible for registration of eligible participants at each study site will fully explain to the participants about the clinical trial before receiving written informed consent from the participants. The coordinators will assign randomized numbers by the sequence of registration to participants to be included in the clinical trial following the inclusion/exclusion criteria who will thus be allocated to either one of the two groups at a 1:1 ratio by opening the sealed envelope in front of the participant. The opened envelopes will be kept separately in a double-lock cabinet. The randomized numbers allocated to each participant will be recorded in the electronic medical chart records.

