##### Credibility and Expectancy Questionnaire

The Credibility and Expectancy Questionnaire [29], which consists of a 9-point Likert scale, will be used for the evaluation of participants’ expectations towards treatment. On the first visit of week 1 (visit 2), participants will choose the score that best answers the following question (1 = not at all, 5 = somewhat, and 9 = very much): “How much do you expect the treatment(s) you will receive during the study period to improve your symptoms?”

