#### Subgroup analysis

Sociodemographic characteristics: body mass index, age (≥ 40 years; and < 40 years), sex, recommendations for surgery, driving, headache, depression, number of sick leave days from work;Physical examination: neurologic examination (sensory loss, muscle weakness), pain upon range of motion (ROM) (i.e. flexion, extension, lateral bending, rotation);Pain characteristics: area of neck pain (bilateral/unilateral, central/trapezius/back), existence of radiating pain (yes/no, unilateral/bilateral, pain under the elbow joint, pain in the back), pain characteristics (acute onset versus slow onset, persistent versus aggravating), conditions of pain aggravation (understress, fatigue), nocturnal pain;Treatment prior to study: experience of Chuna manual therapy, continuation of physical therapy or conventional medication;Expectancy and preference for treatment: credibility and expectancy, preference (Chuna manual therapy; usual care; or no preference);X-ray examination: head forward posture, lateral deviation of spine, cervical intervertebral disc space, degenerative change;Index severity evaluation: VAS ≥ 7 and < 7, NDI high/low.

All statistical analyses were performed with SAS version 9.4 statistical package (SAS Institute, Cary, NC, USA), with the level of significance set at *p* < 0.05.

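### The additional ANCOVA covariates are chosen by baseline significance tests, which leaves the primary model open, passes over site, and could admit treatment expectancy scored after allocation is known

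*Protocol article*

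**What the plan says.** The rule is in the protocol article, Statistical analysis, in the paragraph on the efficacy variable: "Baseline values of each outcome and covariant factors which show statistical difference between groups at baseline will be set as covariates", with treatment group as the fixed factor of the ANCOVA. It covers all the continuous outcomes, including the primary one, neck pain VAS. No other section gives a fixed covariate set or confines this rule to a sensitivity analysis.

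The preceding paragraph describes the baseline comparison: "The sociodemographic characteristics and treatment expectancy of participants will be evaluated by group". For continuous variables "the two groups will be compared using Student’s t-test", with a rank-sum test as the alternative; categorical variables get a chi-square or Fisher's exact test. The closing sentence of Subgroup analysis covers all analyses, "with the level of significance set at" p < 0.05, and no other threshold is given for the baseline tests.

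Three further statements bear on expectancy:

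- Credibility and Expectancy Questionnaire: "On the first visit of week 1 (visit 2), participants will choose the score that best answers the following question".
- Trial design and study setting: "from the second visit onward, participants will receive the neck pain treatment relevant to their random allocation group".
- Randomization and allocation concealment: the allocation is made "by opening the sealed envelope in front of the participant".

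The last of these sections also says that randomization is stratified by site, with equal arms within each of the five sites.

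**The concern.** A baseline significance test in a randomized trial asks whether an imbalance is larger than chance would produce, when chance is known to be the cause. It does not ask whether the variable predicts pain, which is the reason to adjust. A strong predictor that happens to be balanced stays out, and an irrelevant variable that happens to be imbalanced goes in. The model behind the primary result then depends on the data, and two analysts who test different candidate lists could arrive at different primary models.

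The rule also works against the design. Site was used to stratify and so belongs in the model, but blocking within site makes it the factor least likely to show a difference.

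Expectancy raises a separate problem. The trial is open-label. If participants score expectancy once they know their arm, a difference between arms is a consequence of allocation, not a chance imbalance. The rule would then be most likely to bring expectancy into the primary model exactly where that difference is large.

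**Working it through.** **The plan's own figure.** A two-sample t-test with standardised effect 0.6, power 80% and two-sided alpha 0.05 (sidedness is not stated, but two-sided reproduces the figure) needs 45 per arm, with power 0.804. The stated 90 is reproduced. Allowing for 15% gives 45 / 0.85 = 52.9, so 53 per arm or 106, against the stated 108. The checks below use 54 per arm.

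**Chance that a balanced factor enters.** With k independent factors each tested at 0.05, the expected number selected is 0.05k and the chance of at least one is 1 − 0.95^k. The document does not fix k, so it is an assumption. The middle value counts the eight items under the sociodemographic heading in Subgroup analysis, plus expectancy, treated here as recorded before allocation.

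| k | expected number | chance of at least one |
|---|---|---|
| 5 | 0.25 | 22.6% |
| 9 | 0.45 | 37.0% |
| 30 | 1.50 | 78.5% |

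**Site.** The site totals are 24, 22, 22, 22 and 18, which sum to 108. Equal arms within site give 12, 11, 11, 11 and 9 per arm, which sum to 54. At full recruitment the chi-square for site by arm is 0, so the rule cannot select site.

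**Precision.** Assumptions: outcome SD 1, baseline–outcome correlation 0.5, baseline outcome always in the model, and three candidates with a correlation of 0.3 each with the outcome. None of these correlations is in the document.

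- Baseline outcome only: √(2/54 × (1 − 0.25)) = 0.167; simulated 0.165–0.168.
- Selection rule, simulated: about 0.159 with 9 candidates and 0.165–0.166 with 30.
- The three factors prespecified: √(2/54 × (1 − 0.25 − 3 × 0.09)) = 0.133; simulated about 0.134.

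The mean estimates were 0.598–0.602 for a true effect of 0.6, so there was no bias.

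**Error rate and power.** These come from 4,000 simulated trials per setting, with 1 to 20 candidates, all prognostic, and the baseline outcome always included.

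| Model | rejection under the null | power at 0.6 |
|---|---|---|
| Selection rule | 3.2–4.1% | 95.1–96.4% |
| Baseline outcome only | 4.7–5.4% | 94.3–95.2% |
| Same factors prespecified | 4.2–5.2% | about 99% or more |

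The rule is mildly conservative. When a factor is left out, it is known to be fairly well balanced, so the model's standard error overstates the true variability.

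**Expectancy scored after allocation is known.** Let the total effect be d = 0.6 SD, the arm difference in expectancy s SD, and the outcome coefficient c = 0.2–0.3 SD per SD of expectancy (all assumed except d, which is the planning value). With expectancy in the model the estimate targets d − c × s. For s = 0.5 that is 0.6 − 0.2 × 0.5 = 0.50, or 0.6 − 0.3 × 0.5 = 0.45. The table averages over trials in which the rule does and does not select expectancy.

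| s | enters the model | mean estimate | power |
|---|---|---|---|
| 0 | 5% | 0.60 | about 95% |
| 0.3 | 34% | 0.55–0.57 | 91–92% |
| 0.5 | 72–73% | 0.47–0.52 | 81–85% |
| 0.8 | 98% | 0.37–0.45 | 57–71% |

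Without expectancy in the model, power is 94–95% throughout. The row s = 0 also describes scoring before allocation is revealed.

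**The case against.** The best defence is that the rule does little damage. For genuine pre-randomization factors the estimate stays unbiased, the type I error is slightly below nominal, and precision is no worse than with baseline VAS alone. All of that stands, and it limits the severity. It does not rescue the rule, which still leaves the primary model to be settled by the data and bypasses site.

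A reader might infer several stronger things that the document does not support:

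- *Chance decides the whole primary model.* The natural reading keeps the baseline outcome in every model, so chance decides only the additions. The sentence could be parsed as making the baseline outcome conditional too, and should be reworded, but that is the less natural reading.
- *About 30 candidates are tested, so a false selection is nearly certain.* A count that high comes from the subgroup list. The baseline comparison names only sociodemographic characteristics and expectancy, which is nearer nine. The 79% is the upper end of a range.
- *The rule costs a sizeable share of the sample.* Precision is lost only against a prespecified set of real prognostic factors. The document names no such set and gives no correlations, so the loss cannot be fixed from it.
- *The plan adjusts for a post-allocation variable.* Expectancy is never named as a covariate. Secondary outcome measures places registration at visit 2, the visit of the expectancy question, and the text does not say whether the question precedes the opening of the envelope. The figure of assessment timepoints is not available here. The question's future tense fits either order. If it is asked first, expectancy enters about 5% of the time and without bias.

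Nor is this a detail left to an unseen analysis plan. The rule is stated, and an analysis plan that followed it would carry the same fault.

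**Conclusion.** The concern holds in a limited form and should be fixed. The covariates added to the primary ANCOVA are chosen by a test that carries no information on prognosis, from a list that is not closed, and the stratification factor is in effect excluded. The chance of at least one spurious addition runs from 23% to 79% for 5 to 30 independent candidates, with 37% at the most defensible count of nine.

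For true baseline factors the consequence is an unfixed model with little or no gain over baseline VAS alone. It is not bias or a raised false-positive rate.

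The one route to a distorted estimate is expectancy, and it is conditional on scoring after the allocation is known. Under the assumptions shown, an arm difference of 0.5 SD in expectancy would pull the mean estimate from 0.60 to 0.47–0.52 and power from about 94–95% to 81–85%. Those figures show the possible size. They are not a prediction, because neither the order of events nor the shift is stated.

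**What to change.** Delete the baseline-significance rule from Statistical analysis. Specify the primary ANCOVA as treatment, baseline VAS and site, plus any prognostic factors named in advance and measured before randomization. Word it so that the baseline outcome is unconditionally included, and apply the same form to the other continuous outcomes with their own baseline values. Keep expectancy out of the primary model unless it is recorded before the allocation is revealed, and state in the Credibility and Expectancy Questionnaire section which comes first.

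The cost is a few sentences and, for five sites, 4 degrees of freedom. With treatment and baseline VAS only, the residual degrees of freedom are 108 − 3 = 105; with site they are 101, which is immaterial. The sample size of 90, inflated to 108, is unaffected. The change should be made before anyone sees data by arm. The descriptive baseline comparison can stay as it is, provided it no longer determines the model.

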### Sample size

Calculation of number of participants required for the clinical trial: for calculation of significant number of participants, the following is hypothesized based on the previous literature:Level of significance, α = 0.05;Type II error (β) is set at 0.2 with power of the test set at 80%;According to a previous clinical study using VAS as the main assessment tool for Chuna manual therapy in neck pain patients, the effect size of Chuna manual therapy in comparison to the control can be considered to be 1.03 [30], and 1.49 [31], respectively;Compliance rate will be set at 85% (the predicted rate of receiving ≥ 6 sessions of treatment during the five-week treatment period);For calculation of sample size, G*Power 3.1.7 was used. With evidence from item (3), application of mean ± SD resulted in conservatively hypothesizing the effect size of this clinical trial as 0.6 because of the high clinical heterogeneity of manual therapies such as Chuna. Application of items (1) and (2) and the effect size resulted in the calculation of a sample size of 90 participants (45 in each group).The mean comparison of pain requires a total of 90 participants (45 in each group), which is the minimum number of participants needed for testing the abovementioned hypothesis. Considering that 15% of participants received < 6 sessions of treatment within the five-week treatment period, a total of 108 participants, 54 in each group, will be extracted for the study.

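### Allocation is stratified and balanced by site, but the stated ANCOVA leaves site out, so its standard error is somewhat too wide if sites differ after baseline adjustment

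*Protocol article*

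**What the plan says.** Protocol article, Randomization and allocation concealment: "Stratified block randomization will be conducted with stratification by each study site". Site is the only stratification factor named, and "the number of participants in each group will be identical between groups for all study sites". The planned site totals are given: "The number of participants for each study site will be 24 for Jaseng Hospital of Korean medicine Gangnam branch", and "22, respectively for Jaseng Hospital of Korean medicine Bucheon, Daejeon, and Haeundae branches, and 18 for Kyunghee University Korean medicine Hospital at Gangdong".

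Protocol article, Statistical analysis: the efficacy model is an "analysis of covariance (ANCOVA) with the treatment groups designated as the fixed factor". The covariates are fixed by a rule: "Baseline values of each outcome and covariant factors which show statistical difference between groups at baseline will be set as covariates". Site is named neither as a factor nor as a covariate.

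The same section and its Subgroup analysis list mention a repeated-measures ANCOVA, t-tests on the area under the curve, Kaplan–Meier curves with a log-rank test, a Cox model and multiple imputation. Site appears in none of these.

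**The concern.** When arms are equal within every site, differences between site means cancel out of the treatment comparison, so the estimate is already free of them. A model without site does not know this. It leaves the between-site variation in the residual and computes the standard error as if that variation still affected the estimate. The confidence interval is then wider, and the p-value larger, than the randomisation warrants.

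The covariate rule makes this more than an omission that an analysis plan would naturally fill. The rule admits a factor only if the arms differ on it, and the design prevents them from differing on site. An analysis plan that follows the published rule leaves site out; one that includes site departs from the published model. At stake are some precision and a match between the analysis and the way patients were allocated.

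**Working it through.** **Inputs from the article.** Site totals 24, 22, 22, 22, 18, allocated 1:1. Sample size section: "Level of significance, α = 0.05" (sidedness not stated; two-sided assumed), "Type II error (β) is set at 0.2 with power of the test set at 80" per cent, standardised effect 0.6, 15% allowance for non-compliance (treated below as loss), 54 per group.

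**Assumed.** The ICC, meaning the share of outcome variance, after baseline adjustment, that lies between sites. The article gives no figure; 0 to 0.20 is used.

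**1. The plan's own sample size.** A two-sample t-test (noncentral t), two-sided 0.05, d = 0.6, needs 45 per group, with power 0.804. This matches the stated 90; a one-sided test would need 36. Allowing for 15%: 45 / 0.85 = 52.9, so 53 per group or 106, against the stated 108. The figure reproduces, and it takes no credit for stratification.

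**2. Can site enter by the covariate rule?** 24 + 3 × 22 + 18 = 108. All totals are even, so each arm has 12, 11, 11, 11 and 9. The site-by-arm chi-square is exactly 0 (p = 1).

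**3. Analytic size of the effect.** With total residual variance 1, the within-site variance is 1 − ICC and the between-site variance is ICC. Without site the model has 108 − 3 = 105 residual degrees of freedom (intercept, treatment, baseline). Its expected residual mean square is approximately (1 − ICC) + k × ICC, where

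k = (N − Σn²/N) / 105, with Σn² = 576 + 3 × 484 + 324 = 2352,

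k = (108 − 2352/108) / 105 = (108 − 21.78) / 105 = 0.821.

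Hence SE ratio (without site / with site) = √(1 + 0.821 × ICC / (1 − ICC)):

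- ICC 0.05: √1.0432 = 1.021
- ICC 0.10: √1.0912 = 1.045
- ICC 0.20: √1.2053 = 1.098

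Multiplying the critical value 1.983 (105 df) by these ratios and reading the two-sided tail on 101 df gives type I errors of about 0.045, 0.041 and 0.032.

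**4. Simulation, complete data.** 8,000 trials per scenario, planned site sizes, exact 1:1 split, residual SD 1 given baseline, no true effect.

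| ICC | Mean SE, no site | Mean SE, with site | Ratio | Type I, no site | Type I, with site |
|---|---|---|---|---|---|
| 0 | 0.193 | 0.193 | 1.00 | 0.050 | 0.050 |
| 0.05 | 0.192 | 0.188 | 1.02 | 0.045 | 0.049 |
| 0.10 | 0.191 | 0.183 | 1.04 | 0.041 | 0.048 |
| 0.20 | 0.189 | 0.173 | 1.09 | 0.032 | 0.050 |

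The actual spread of the estimate is the same under both models: SD 0.182 at ICC 0.10 and 0.173 at 0.20. The site-free SE is therefore too wide by 0.191/0.182, about 5%, and 0.189/0.173, about 9%. The SE with site agrees with the actual spread.

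Simulation error is √(0.05 × 0.95 / 8000) = 0.0024 for these type I errors. A run at ICC 0.02 gave 0.056 without site and 0.057 with it. Both models moved together, and the with-site test is exact under the simulated normal errors, so this is read as simulation noise. The formula in step 3 gives 0.048 for the site-free model there.

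**5. Power at d = 0.6 with 15% random loss.**

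| ICC | Without site | With site |
|---|---|---|
| 0 | 0.802 | 0.799 |
| 0.05 | 0.811 | 0.819 |
| 0.10 | 0.824 | 0.842 |
| 0.20 | 0.838 | 0.877 |

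Simulation error is about 0.004 per entry, but both models were fitted to the same data sets, so the differences are steadier than that. Loss disturbs the exact balance; the direction does not change.

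**The case against.** The strongest case on the other side is that nothing is invalid and little is lost. The error is conservative, and the sample size was set for a plain two-group comparison at 80% power with no gain from stratification. Site-free power stays at or above that level throughout the table. This stands. A reader might infer an inflated false-positive rate or an underpowered trial; the calculations show neither.

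The size rests on an ICC that the documents do not give. This also stands. What counts is site variation remaining after the baseline value is in the model, so site differences that baseline explains do no harm. It would go too far to say that the standard error is wrong whenever sites differ.

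A reader might also infer that the repeated-measures ANCOVA, log-rank test, Cox model and imputation are misspecified. The article names them but gives no separate factors, strata or imputation variables. A journal article commonly leaves these to the analysis plan, and the calculations above cover only the ANCOVA. Only the ANCOVA sentence is explicit enough to be criticised.

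Another tempting argument is that practitioners of manual therapy differ between sites. Chuna practitioners treat only the Chuna arm, so such differences would appear mainly as treatment-by-site variation, which a site main effect does not model. The article also requires at least three years of Chuna experience and standardising training. That argument is not relied on here.

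Finally, it is slightly too strong to say that site could never qualify under the covariate rule. Dropping participants who received no session, or loss to follow-up, can disturb the balance. A significant site imbalance would still be very unlikely.

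**Conclusion.** The point holds as a mismatch between design and stated analysis: site governs the allocation, but the ANCOVA has treatment as its only factor and a covariate rule that in practice keeps site out. The consequence is a conservative test and confidence intervals that are somewhat too wide, modest at low ICC and disappearing if sites do not differ after baseline adjustment. In power, the loss is about 1 percentage point at ICC 0.05, 2 at 0.10 and 4 at 0.20.

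These sizes assume normal errors, a common treatment effect across sites, loss at random, and an effect of 0.6 measured against the SD after baseline adjustment. The comparison between the two models matters more than the absolute power levels. This should be corrected, but it does not threaten the trial's validity or its planned sample size.

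**What to change.** Add site, five levels and fixed, to the primary ANCOVA alongside treatment and the baseline value, and state that it is included because allocation was stratified by it, whatever the baseline comparison shows. The cost is 4 residual degrees of freedom (105 to 101). With no site variance the simulated power is unchanged with complete data (0.866 under both models) and 0.802 against 0.799 with 15% loss, a difference within simulation error. Sample size and trial procedures stay as they are.

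For consistency, also carry site into the repeated-measures ANCOVA and the imputation model, and stratify the log-rank test and Cox model by site. For these it is a matter of completing the specification. All of this needs only wording in the analysis plan, settled before the statistician is unblinded.
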